### Withdrawal procedures

It will be made clear to patients that they can withdraw from the study at any time and return to the standard of care. However, any data collected up to the time of withdrawal will be included if participants agree to it.

### Proposed outcome and statistical analyses

#### Prediction performance (Objective 1)

The diagnostic accuracy of each of the three mpMRI predictive variables (T2WI (5-point ordinal scale), DWI (5-point ordinal scale) and DCE-MRI (2-point ordinal scale)) will be evaluated through logistic regression with PCa as the binary outcome (Yes/No). The T2WI and DWI will be dichotomised by assigning 0 to scores of 1–2 and assigning 1 to scores of 3–5 [11], and presented as percentages and denominators in the tables. The predictive performance of the dichotomised variables for the diagnosis of PCa will be analysed both individually and by considering all possible combinations among them. Additional variables as potential predictors in the logistic regression model will also include age, stage and comorbidity. Predictive ability will be estimated from the area under receiver operating characteristic (AUROC) curves drawn from the estimated probabilities given by the corresponding logistic regression models. Accuracy will be assessed by implementing the Hosmer–Lemeshow test for calibration. A score algorithm will be derived from the final logistic regression model.

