## Methods/design

### Study population and setting

Prospective recruitment of men referred with suspected clinically localised PCa will be carried out in urology clinics. The number of patients screened for eligibility over the recruitment period is estimated to be 1000. The number of patients not eligible for the study is estimated to be 350 and the number of patients who are likely to decline is estimated to be 50. The number of participants who are likely to progress to pre-biopsy MRI is estimated to be 600. Local audit information suggests that after a positive diagnosis of PCa, around 25% of men will opt for radical surgery. Based on the recruitment of 600 eligible men, the lowest amount of complete data for radical prostatectomy histology for analysis will be *n* = ~ 150. Our power calculation based on 80% sensitivity and a precision of ± 9% and an AUROC = 0.9 suggests that we need a minimum of 80 men with complete datasets from imaging and histopathology of radical prostatectomy to answer the primary objective. The dropout rate and incomplete datasets have been taken into consideration in designing this study.

Rais-Bahrami et al. [8] suggest that 80% of all pre-biopsy MRI scans (*n* = ~ 600) will have lesions suspicious for PCa, regardless of the level of suspicion assigned by mpMRI (*n* = ~ 480). Based on such information, we calculated that each of the two randomisation arms will have approximately 240 patients.

Initially, the total duration of the recruitment phase was 48 months; however, this will now be extended to 66 months with approval from the funding body. It is estimated that approximately 600 participants will be recruited and will receive a pre-biopsy MRI scan.

Participants will then be divided into two groups based on the mpMRI results. The group with positive mpMRI (*n* = ~ 480) will be randomised to the intervention (TRUS and MRI/US fusion-guided biopsy) group (*n* = ~ 240) or the standard care (TRUS-guided biopsy) group (*n* = ~ 240). The group with negative mpMRI (*n* = ~ 120) will undergo standard care (TRUS-guided biopsy) with histological comparative analysis. Participants will be followed through to a definite treatment stage. At sites where local facilities allow and for those who will undergo radical prostatectomy, histological findings will be compared to the pre-biopsy MRI results (*n* = ~ 80). The active trial participation for each participant will be varied depending on sites’ local pathways.

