### Allocations and interventions

All enrolled participants will be offered 1.5 Tesla or 3.0 Tesla mpMRI prior to prostate biopsy where this is not already within the standard care pathway. A subgroup of participants with positive pre-biopsy MRI will be randomised into two further subgroups at a 1:1 ratio. Randomisation will be via TRUST, a web-based, good clinical practice (GCP)-compliant randomisation system run by the Health Informatics Centre (HIC). Randomisation will be implemented with random block sizes stratified by site and minimised by: the Prostate Imaging Reporting and Data System (PI-RADS) suspicion score (3–5); index lesion size (in two categories: above and below 6 mm in maximal diameter on MRI); age (40–59 years, 60–75 years); and PSA < 10.1 or PSA ≥ 10.1 to ≤ 20 ng/ml). The first subgroup will undergo a TRUS and MRI/US fusion-guided biopsy and the second will undergo standard of care TRUS-guide biopsies only. The MRI/US fusion-guided biopsy will be performed during the same attendance as the TRUS-guided biopsy***.*** TRUS and MRI/US fusion-guided biopsies will be performed by NHS-accredited radiologists and/or urologists from the research team. The persons undertaking the biopsy will have prior experience and will have received appropriate training from clinical experts and/or the equipment supplier’s application specialist(s). Those participants with negative pre-biopsy MRI will follow the local standard of care pathway; where this includes biopsy, data from the biopsy will be collected for analysis.

In a subgroup of patients who undergo radical prostatectomy, the prostatectomy specimen will be sectioned using customised moulds [9, 10] allowing for direct comparison with mpMRI. This will be carried out in NHS Tayside, NHS Grampian and other sites where local facilities allow. Comparison of mpMRI with a reference standard of radical prostatectomy pathology will be performed as the primary outcome.

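### Read per man, the Objective 1 model for PCa Yes/No has essentially no non-cases in the prostatectomy reference set, so the 80 men support sensitivity but not the AUROC of 0.9

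*Protocol article*

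**What the plan says.** Four statements in the protocol article bear on this point.

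- **Reference standard.** Both primary outcome measures under Objectives (PCa detected, clinically significant PCa detected) are set against prostatectomy specimens. Allocations and interventions repeats it: "Comparison of mpMRI with a reference standard of radical prostatectomy pathology will be performed as the primary outcome".
- **Who is in the reference set.** Study population and setting: "Local audit information suggests that after a positive diagnosis of PCa, around 25% of men will opt for radical surgery".
- **Size and counting unit.** The same section states: "Our power calculation based on 80% sensitivity and a precision of ± 9% and an AUROC = 0.9", concluding that "we need a minimum of 80 men with complete datasets from imaging and histopathology of radical prostatectomy to answer the primary objective".
- **Analysis.** Prediction performance (Objective 1) says that diagnostic accuracy "will be evaluated through logistic regression with PCa as the binary outcome (Yes/No"). It continues: "Predictive ability will be estimated from the area under receiver operating characteristic (AUROC) curves", and "Accuracy will be assessed by implementing the Hosmer–Lemeshow test for calibration". A score algorithm is then to be derived from the final model.

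The Objective 1 section does not itself name the reference standard, the unit of analysis or any allowance for clustering. The link to prostatectomy comes from the other three places. Comparing biopsy results between MRI-negative and MRI-positive men appears only as a secondary outcome under Objective 2.

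**The concern.** A logistic model, an AUROC and a calibration test all need men with and without the outcome. The stated reference standard is available only for men who have already been diagnosed with PCa and then chose surgery. If the man is the unit, the outcome is essentially constant in the set that is meant to answer the primary objective.

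At stake are the main accuracy model, its AUROC and calibration, the derived score, and the AUROC part of the sample-size justification. If the mismatch is left open, the unit, the outcome or the reference standard has to be chosen later, possibly with the data in view. Each choice answers a different question.

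**Working it through.** **Inputs.** From Study population and setting: sensitivity 0.80, precision ±0.09, AUROC 0.9, 80 men, and surgery after a positive diagnosis. From the Objective 1 section: outcome PCa Yes/No. The confidence level is not stated; 95% two-sided (z = 1.96) is assumed.

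**1. The plan's own figure.** Precision of a single proportion: n = z²p(1−p)/d² = 1.96² × 0.8 × 0.2 / 0.09² = 75.9, so 76 men. In reverse, 80 men give 1.96 × √(0.8 × 0.2/80) = 0.0877, or ±8.8%, which rounds to the stated ±9%. The figure of 80 is compatible with the sensitivity inputs, and all 80 men count as cases in that calculation.

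**2. The AUROC in the prostatectomy set, per man.** AUROC is a probability over case/non-case pairs. With 80 cases and 0 non-cases there are 80 × 0 = 0 pairs, so it is undefined. Specificity has a denominator of 0. At the article's projected ~150 men there are 150 × 0 = 0 pairs, so a larger surgical set does not help.

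**3. The logistic model.** When every outcome equals 1, the likelihood keeps rising as the intercept grows, and no finite estimate exists. A test fit on 80 such men did not converge: the intercept stopped near 26 with a standard error of about 140,000, and slope standard errors exceeded 450,000. The Hosmer–Lemeshow test has no outcome variation to work on, and no score can be derived.

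**4. If some observations are negative.** The article gives no case/non-case split, so the splits below are assumptions. The Hanley–McNeil variance is

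Var = [A(1−A) + (n₁−1)(a−A²) + (n₀−1)(b−A²)] / (n₁n₀),

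with A = 0.9, a = A/(2−A) = 0.8182 and b = 2A²/(1+A) = 0.8526.

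Example at 76/4: [0.09 + 75 × 0.00818 + 3 × 0.04263]/304 = 0.002735. The standard error is 0.0523 and the half-width is 1.96 × 0.0523 = 0.103.

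| Cases / non-cases (80 independent units) | 95% half-width for AUROC 0.9 |
|---|---|
| 80 / 0 | undefined |
| 79 / 1 | ±0.188 |
| 78 / 2 | ±0.137 |
| 76 / 4 | ±0.103 |
| 72 / 8 | ±0.080 |
| 60 / 20 | ±0.067 |
| 40 / 40 | ±0.071 |

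One or two specimens without residual tumour would make the AUROC computable, but with a half-width of ±0.14 to ±0.19. Regions or lesions within one man are not independent, so they would need a further allowance.

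**The case against.** The strongest reply is that the difficulty is conditional. It arises only if the unit is the man and the reference for this model is prostatectomy, and the Objective 1 section states neither.

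- **Region-level reading.** Specimens are sectioned in customised moulds so that they can be matched to MRI. Spatial matching yields cancer-positive and cancer-negative regions, and such an analysis could also be sized in men. This stands as a possibility. The article names no such unit and no clustering, sizes the set in men, and lists age and comorbidity, which are patient-level, among the predictors.
- **Biopsy-referenced reading.** The model could be fitted in all biopsied men. This too is computable, but it conflicts with the primary reference fixed in three other places. MRI-negative men are biopsied only where the local pathway includes it.
- **Detail left to the full protocol or analysis plan.** A unit of analysis may well be defined there. But the outcome and the reference population stated here conflict when read per man. A further document can resolve that only by specifying a different unit, outcome or reference.
- **Tumour-free specimens.** The exception is real, and step 4 shows how little it helps.

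A reader might infer more than the article supports. It does not follow that Objective 1 cannot be analysed at all, because two computable readings exist. Nor does it follow that the sample size of 80 is wrong. The Background's figure of up to 35% false-negative first biopsies should not be carried over to a biopsy-referenced analysis here. It is an upper figure for TRUS-guided biopsy, and about 240 men would also have fusion biopsy.

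**Conclusion.** The point holds in conditional form. With prostatectomy histology as the reference and the man as the unit, the PCa Yes/No model, AUROC, Hosmer–Lemeshow test and score have essentially no non-cases. The 80 men support sensitivity at about ±8.8%; they do not support the AUROC of 0.9 quoted beside it.

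This rests on reading the primary reference from Objectives, Study population and setting, and Allocations and interventions, on surgery following diagnosis as the article describes, and on a 95% level. It does not depend on whether 76 or 80 is the exact number.

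Two further inferences should be avoided. Clinically significant cancer, the second primary outcome, could supply both classes among surgical patients, but the article gives no figure for its split there. Nor does the article show that T2WI, DWI and DCE scores are recorded by region, so a region-level analysis cannot be assumed to need only extra data entry.

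The mismatch concerns the primary analysis and should be resolved before that analysis is run.

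**What to change.** 1. **Prostatectomy set, per man.** State sensitivity as the primary estimate, with the ±9% precision as its basis. Remove the per-man PCa Yes/No AUROC as a justification for the 80 men.
2. **AUROC and specificity against prostatectomy.** Obtain them from a region- or lesion-level analysis on the mould-aligned sections, with clustering within men accounted for and the MRI scores used at the level already recorded. Add a per-man model of clinically significant versus non-significant PCa. State that its AUROC will be imprecise if non-significant cancers are rare (about ±0.10 at an assumed 76/4 split).
3. **All biopsied men.** Label any PCa Yes/No model and score in this group as secondary and biopsy-referenced.

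**Cost.** Mostly wording of the analysis section. Clustered intervals will be wider than simple region counts suggest. Region-level specificity will describe only men selected for surgery, not all referred men. If scores were not recorded by region, extra coding is needed and may mean re-reading scans; Trial status reports 416 men already recruited, although only those who have surgery would be affected.

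### The Objective 1 analysis names no single mpMRI positivity rule, reports no sensitivity against prostatectomy, and gives clinically significant cancer no analysis

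*Protocol article*

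**What the plan says.** The protocol article describes the primary objective in four places.

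- **Objectives** lists two primary outcomes: how many prostate cancers, and how many clinically significant cancers, mpMRI detects when judged against prostatectomy specimens.
- **Allocations and interventions** treats mpMRI as one test: "Comparison of mpMRI with a reference standard of radical prostatectomy pathology will be performed as the primary outcome".
- **Study population and setting** gives the planning basis: "Our power calculation based on 80% sensitivity and a precision of ± 9" per cent. The same sentence adds an AUROC of 0.9 and arrives at a minimum of 80 men with complete imaging and prostatectomy data. This section also splits all participants by mpMRI result into about 480 positive and 120 negative.
- **Prediction performance (Objective 1)** gives the analysis. "The diagnostic accuracy of each of the three mpMRI predictive variables", namely T2WI, DWI and DCE-MRI, "will be evaluated through logistic regression with PCa as the binary outcome (Yes/No"). Then: "The T2WI and DWI will be dichotomised by assigning 0 to scores of 1–2 and assigning 1 to scores of 3–5". The section continues: "The predictive performance of the dichotomised variables for the diagnosis of PCa will be analysed both individually and by considering all possible combinations among them". Performance is summarised by AUROC from fitted probabilities and by the Hosmer–Lemeshow test, and a score is derived from the final model. Age, stage and comorbidity may also enter as predictors.

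**The concern.** A count of cancers detected by mpMRI, or a sensitivity, needs one rule that turns each mpMRI into positive or negative. The trial has an overall result of this kind, because it decides which men are randomised. The Objective 1 analysis does not use it. It assesses the component sequences, and nothing says which of them, or which combination, stands for mpMRI. The score from the final model has no threshold. The outcome variable is any prostate cancer, so the second primary outcome does not appear at all.

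An analyst who followed the section faithfully would report AUROCs, a calibration test and a score. The sensitivity that the sample size was built on would be missing, and so would any result for clinically significant cancer. With no primary index test fixed in advance, the sequence set that performs best could be presented as the result for mpMRI.

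**Working it through.** **1. The plan's own sample size.** Inputs from Study population and setting: sensitivity p = 0.80, precision d = 0.09, n = 80. The confidence level is not stated; 95% two-sided is assumed.

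- n = z²p(1 − p)/d² = 1.96² × 0.80 × 0.20 / 0.09² = 75.9, so 76. Other interval methods give 75 (Wilson), 85 (Clopper–Pearson) and 87 (Wald with continuity correction). An assumed 5% loss gives 76/0.95 = 80.
- In reverse, at n = 80 the half-width is 1.96 × √(0.80 × 0.20/80) = 0.0877, or 8.8 points, which rounds to 9.

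The simple formula does not return 80 exactly, but 80 men are consistent with ± 9% and this is not an error. The precision belongs to one proportion, that is, one prespecified positive/negative call. With the same n the half-width is 10.0 points at 70% sensitivity and 6.6 at 90%.

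**2. Number of candidate index tests.** Three variables, one main-effects model per non-empty set: 3 singles + 3 pairs + 1 triple = 2³ − 1 = 7. Four of these are combinations in the strict sense.

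**3. Whether AUROC can stand in for sensitivity.** For one dichotomised variable, AUROC = (sensitivity + specificity)/2. An AUROC of 0.9 then fits 80% sensitivity with 100% specificity, 100% with 80%, or anything between. Once age, stage or comorbidity is in the model, the AUROC is no longer that of mpMRI alone.

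**4. Stated outcome against stated analysis.**

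| Element | Objectives, design and sample size | Prediction performance (Objective 1) |
|---|---|---|
| Index test | mpMRI as one test | Three sequences, up to seven sets |
| Measure | Cancers detected; sensitivity 80% ± 9%, and AUROC 0.9 | AUROC, Hosmer–Lemeshow, score without threshold |
| Target condition | Any cancer; clinically significant cancer | Any cancer only |

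Only the AUROC and the any-cancer endpoint match.

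**5. Where the overall result is analysed.** Randomised controlled trial (Objective 2) lists a secondary outcome that compares MRI-negative with MRI-positive men on TRUS biopsy histology. The reference there is biopsy, not prostatectomy.

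**6. A constraint on the remedy.** Identifying potential participants allows recruitment after a standard-care mpMRI only if it was positive. For those men patient-level sensitivity is 100% by selection. If a share f of the analysed men entered this way and true sensitivity is 80%, the pooled estimate is f + (1 − f) × 0.80. The documents do not give f. For illustration, f = 0.25 gives 0.25 + 0.75 × 0.80 = 85%, and f = 0.50 gives 0.50 + 0.50 × 0.80 = 90%.

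**The case against.** The best defence is that the article condenses a fuller protocol, and that a threshold or a model-selection rule may properly sit in the analysis plan. The section also connects with the outcome in several ways. The sample-size sentence cites an AUROC as well as a sensitivity. One final model is intended, and the three-sequence model is itself a composite reading of mpMRI. The dichotomised T2WI and DWI are to be tabulated as percentages with denominators, so some per-sequence detection can be read off.

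All of that stands, and it limits the point. It does not remove it: the article fixes one set of index tests, measures and outcomes for an objective that it defines elsewhere with another. A plan that only filled in detail beneath this section would still lack the sensitivity and the second endpoint.

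Three stronger readings are tempting, and the documents do not support them.

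- *That PI-RADS 3–5 is the trial's definition of a positive mpMRI and the analysis ignores it.* PI-RADS appears once, as a minimisation factor, "the Prostate Imaging Reporting and Data System (PI-RADS) suspicion score (3–5"), among men already MRI-positive. The cut is implied there and matches the one used per sequence, but it is not stated as the definition. The estimate of about 480 positives even counts suspicious lesions at any level of suspicion.
- *That the accuracy of the overall call is estimated nowhere.* The secondary comparison against TRUS biopsy uses it. What is missing is its accuracy against prostatectomy.
- *That the loss can be sized by contrasting an any-positive with an all-positive rule.* With 70% sensitivity per sequence and independent misses, these give 1 − 0.3³ = 97% and 0.7³ = 34%; with 80%, 99% and 51%. The inputs are assumed, independence is doubtful for sequences that image the same lesion, and the plan combines sequences by regression. These figures do not measure an error in this plan.

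**Conclusion.** The point holds as a mismatch between the stated primary outcome and the only analysis stated for it. Three things are absent from that analysis: a single primary rule for a positive mpMRI, its sensitivity against prostatectomy, and any analysis of clinically significant cancer. In their place stand up to seven sequence sets judged by AUROC and calibration.

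Its size is structural: of the two primary outcomes, one has no analysis, and the other has one that does not yield the planned sensitivity. The sample size is not in doubt. Eighty men support ± 8.8 points at 80% sensitivity, assuming a 95% two-sided interval, independent men and one prespecified call. This deserves correction before analysis, but it does not call the trial's design into question.

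**What to change.** In Prediction performance (Objective 1):

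1. Name the overall positive/negative mpMRI result that already divides participants as the primary index test, with the sponsor stating its cut-off.
2. Report its sensitivity with a 95% CI against prostatectomy histology, separately for prostate cancer and for clinically significant prostate cancer.
3. Make the sequence combinations, their AUROCs and the score algorithm secondary.
4. State the unit of analysis. Either run the primary analysis by lesion or sector, which the customised moulds make possible by allowing direct comparison with mpMRI, using intervals that allow for several lesions or sectors per man; or exclude men who entered through the positive-mpMRI route from any patient-level sensitivity.

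The cost is wording and a little more analysis. No new sample size is needed for the index test itself, and the overall result should exist for every participant. The minimisation record alone would not supply it, because it covers only randomised MRI-positive men. If men are excluded, the interval widens somewhat. For illustration, if 60 of 80 men remained (an assumed number), the half-width at 80% would be 1.96 × √(0.16/60) = 10.1 points instead of 8.8.

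### The Hosmer–Lemeshow test is named as the accuracy measure for the mpMRI models, but it is empty for each single dichotomised variable and leaves the score's calibration without a usable measure

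*Protocol article*

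**What the plan says.** The section *Prediction performance (Objective 1)* of the protocol article sets out the analysis in this order.

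- **Coding.** "The T2WI and DWI will be dichotomised by assigning 0 to scores of 1–2 and assigning 1 to scores of 3–5". DCE-MRI is already on a two-point scale, so all three mpMRI variables are binary.
- **Models.** "The predictive performance of the dichotomised variables for the diagnosis of PCa will be analysed both individually and by considering all possible combinations among them".
- **Further candidates.** "Additional variables as potential predictors in the logistic regression model will also include age, stage and comorbidity".
- **Discrimination.** "Predictive ability will be estimated from the area under receiver operating characteristic (AUROC) curves drawn from the estimated probabilities", for each corresponding model.
- **Accuracy.** "Accuracy will be assessed by implementing the Hosmer–Lemeshow test for calibration".
- **Product.** A scoring rule is then built from the final model.

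The section gives no sample size for the regression, no number of Hosmer–Lemeshow groups, no significance level and no rule for acting on the result. It names no other calibration measure. *Study population and setting* sizes the primary objective on a sensitivity of 80% with precision ±9% and an AUROC of 0.9, and concludes that "we need a minimum of 80 men with complete datasets from imaging and histopathology of radical prostatectomy to answer the primary objective". It expects about 150 such men. *Allocations and interventions* makes prostatectomy pathology the reference standard for the primary outcome.

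**The concern.** Hosmer–Lemeshow is a goodness-of-fit test of calibration. It asks whether fitted and observed risks differ by more than chance within groups of the fitted risk. Three things make it a poor choice as the named measure of accuracy here.

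1. With a single binary predictor there is nothing left to test, because the model reproduces the data it is tested on.
2. With several predictors and a small sample, a non-significant result is weak evidence of good calibration.
3. The test uses the men who were used to fit the model. It cannot show whether predicted risks will be too extreme in new men, which is the main risk for a score chosen after many combinations have been tried.

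At stake is a published score described as accurate or well calibrated on evidence that cannot support this. The quantity on which the trial was sized, sensitivity, is not named as the accuracy measure in the analysis section.

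**Working it through.** **The plan's own size.** Inputs from *Study population and setting*: sensitivity 0.80, precision ±0.09. A 95% confidence level is assumed, as none is stated. n = z²p(1−p)/d² = 1.96² × 0.8 × 0.2 / 0.09² = 75.9, so 76 against the stated 80. At n = 80 the half-width is 1.96 × √(0.16/80) = 8.8%, which rounds to 9%. The stated 80 is a slightly cautious rounding, not an error. The expected number reproduces: 600 × 25% = 150.

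**One binary predictor.** Let n₁ units be positive with y₁ cancers, and n₀ negative with y₀ cancers. The model has two parameters and two covariate patterns, so the fitted risks are y₁/n₁ and y₀/n₀. Each group contributes (observed − expected)² in the numerator, and expected = n₁ × (y₁/n₁) = y₁, likewise for y₀. The statistic is therefore 0, on 2 − 2 = 0 degrees of freedom, and no p-value exists. Simulation agrees: over 1,000 runs per setting at n = 80, 150 and 600, with a useless, good or reversed predictor, the largest value was 4 × 10⁻¹¹, which is numerical error.

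**Two or three binaries.** Main-effects models have at most 4 or 8 covariate patterns and 3 or 4 parameters, which leaves 1 or 4 degrees of freedom. The only misfit such a test can see is an omitted interaction.

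**Chance of detecting misfit.** Simulated logistic fits: about 10 groups with ties kept together, groups − 2 degrees of freedom, 5% level assumed, 1,500 runs per scenario. The rejection rate for a correct model was 4% to 5%.

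| Misfit | n = 80 | n = 150 | n = 600 |
|---|---|---|---|
| Two binaries, omitted interaction of −2 logits | 34% | 61% | 99.9% |
| Three binaries, omitted interaction of −2 logits | 16% | 33% | 98% |
| Three binaries plus age, omitted interaction of −2 logits | 10% | 15% | 53% |
| Omitted quadratic in age | 5% | 6% | 18% |
| True five-point effect fitted as dichotomised | 4% | 4% | 3% |
| One continuous predictor, strong curvature | 57% | 90% | 100% |

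A separate run of the three-binary model with smaller omitted interactions (+1.1 and −1.5 logits) gave detection of about 5% and 7% at n = 80, 7% and 16% at n = 150, and 43% and 84% at n = 600.

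**Overfitting.** Final model of three binaries, age and comorbidity; 800 runs; true calibration slope measured in 4,000 new men. Assumptions: outcome prevalence about 40% to 50% and latent correlation 0.5 between sequences. A slope of 0.8 serves only as an illustrative mark.

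| | n = 80 | n = 150 | n = 600 |
|---|---|---|---|
| Median slope in new men | 0.63 | 0.78 | 0.94 |
| Slope below 0.8 | 78% | 54% | 9% |
| Test not significant, given slope below 0.8 | 97% | 97% | 96% |

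A second simulation, with assumed effects from moderate to very strong, gave median slopes of 0.53 to 0.81 at n = 80 and 0.73 to 0.89 at n = 150. The test was non-significant in 92% to 97% of the models with slope below 0.8. The amount of overfitting depends on the assumed effects; the test's blindness to it hardly does.

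**What AUROC adds.** Mean apparent AUROC for a useless single binary was 0.54 at n = 80 and 0.53 at n = 150. For a useless model of three binaries plus age it was 0.62 and 0.59. The design value is 0.9.

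**The case against.** The strongest reply is that the sentence should not be read alone. AUROC is planned immediately before it, and the test is described as being for calibration, so accuracy may simply be loose wording. This stands. A reader might infer that a useless mpMRI model would pass the whole assessment. The article does not support that: AUROC would show such a model at about 0.53 to 0.62, and no decision is tied to the Hosmer–Lemeshow result.

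Nor is it right to say that single-variable models always pass. With 0 degrees of freedom nothing is tested, and such a model cannot be miscalibrated in its own data. The sentence may also be meant only for the final model, next to which it stands. If so, the point about single variables falls away, but small-sample weakness and overfitting remain.

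The sample size is also open. Men who had prostatectomy after a positive diagnosis all have cancer, so a Yes/No model needs either lesions or regions as units, or biopsy outcomes in up to about 600 men. Detection of interactions is much better at 600. A claim that the test misses most misfit in general would go too far, since detection ran from 4% to 90% at 80 to 150.

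Finally, the number of groups, plots and internal validation belong in an analysis plan that is not shown. Their absence is not the point. The point is a method that the article states and that cannot do what it is named for.

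**Conclusion.** The point holds in a limited form and merits a change. For each single dichotomised variable the test carries no information; this is algebra and holds at any sample size. For the multi-variable models, if 80 to 150 units are analysed, it is weak against most moderate misfit (mostly 4% to 34% detection) but not against gross misfit. Run on the fitting data, it cannot reveal overfitting of the score. AUROC covers discrimination, so what lacks a usable measure is the calibration of the score, not the whole evaluation of mpMRI.

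The simulated figures rest on an assumed 5% level, about 10 groups, the chosen forms of misfit, and an analysis unit that has both outcomes. The overfitting figures also rest on the assumed prevalence, correlation and effect sizes. At about 600 units the concern about interactions and overfitting shrinks substantially; the emptiness for single variables does not change.

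**What to change.** Replace the Hosmer–Lemeshow sentence with two statements.

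1. For each dichotomised variable and each combination, accuracy is reported as sensitivity and specificity with 95% confidence intervals. Sensitivity is the quantity on which the trial was sized. The unit of analysis should be stated, because specificity can be estimated only where some units are free of cancer.
2. For the final score only, report the bootstrap optimism-corrected calibration slope and intercept with 95% confidence intervals and a calibration plot, repeating the selection of the final model in each resample. Good calibration is not to be inferred from a non-significant Hosmer–Lemeshow test.

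AUROC stays as planned. The cost is one revised sentence and a little more programming, with no new data. The downside is that at 80 to 150 men the interval for the slope will be wide, so calibration of the score may have to be reported as not established.
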